## 1.1 Study Rationale

This study is undertaken in order to gather clinical data on the use of the newly developed Navina System. The main objective is to evaluate the change in NBD symptoms after 3 months use of Navina Smart. The study will include patients with confirmed NBD refractory to conservative therapy and judged eligible for transanal irrigation.

Since the product is CE-marked based on similarities to existing products it is concluded that there is no need to conduct a study for regulatory purposes and thus a single arm study design has been chosen. However, in order to assure healthcare professionals and users that the product and concept is effective, reliable and safe, it is essential to conduct a sufficiently powered clinical study with clinically relevant endpoints. In addition, the study is intended to assess whether the enhanced functionality of the Navina Smart system, in terms of flexibility in tailoring irrigation regimes, is associated with enhanced outcomes and greater patient tolerability. Further, from a post-market surveillance perspective it is considered important to conduct this study in order to satisfy possible future ethical and regulatory demands.

In a randomized controlled trial investigating TAI, it was observed that the frequency of urinary tract infections (UTIs) with prescribed antibiotics were significantly lower in the group using TAI (5.9%) compared to the group using conservative therapy (15.5%). The mechanism in the interaction between bladder and bowel dysfunction is complex and not yet understood. This study will further investigate these findings.

## 1.2 Risk/Benefit Assessment

There are several side effects or problems reported with the use of TAI, though most of them are mild and of minor concern. These complications should be viewed in the light of complications related to NBD, such as severe constipation, faecal incontinence and/or bowel-related surgical procedures.

Rectal perforation is considered the most serious side effect and the estimated incidence (from 2009) of rectal perforation due to TAI is 0,002% (one per 50 000 procedures). However, the latest data on perforation indicates a decrease to 0.0002% (one per 500 000 procedures). This may be compared to the risk for rectal perforation due to colonoscopy; 0,1% (one per 1000 procedures) and flexible sigmoidoscopy; 0,0025% (one per 40 000 procedures) respectively.

In the context of TAI with a rectal balloon catheter, perforation of the rectum may occur due to 3 major causes;

- Direct impaling trauma
- Over-inflation of the balloon
- Exaggerated hydrostatic pressure during water instillation

Perforations due to direct impaling trauma will most often be located in the rectum or in the anal canal. If the perforation affects only the extra-peritoneal perirectal space it is possible that the event will be asymptomatic and stay unrecognized. It is possible that this event may not necessitate surgery, but drainage and antibiotics instead. Should however, the intra-peritoneal space be affected, it is considered as an acute medical emergency condition that most often requires abdominal surgery with the formation of a stoma.

At the ISCOS meeting in October 2013 the company Coloplast A/S (Denmark) held a symposium regarding bowel perforations due to the use of TAI with their device Peristeen®. They reported 46 rectal perforations since the introduction of the product, and with a sudden increase of events in 2010 and 2011. After some alterations in catheter design (e.g. catheter tip, balloon) and properties (e.g. stiffness and flexibility) the event rate decreased, according to Coloplast, the following years. From the presented data it is evident that the vast majority of the perforations occur in the rectum (~ 46%), that there is almost an equal distribution between sub- and intra-peritoneal relation, and that almost 70% of the cases are treated with the formation of a stoma. Out of the 46 reported cases, the outcome was fatal in three of them (6.5%). The overall experience gathered by Coloplast led them to state that approximately 60% of perforations will occur within the first five weeks of use and that the perforation rate is not cumulative (i.e. increasing over time). Prior surgery to or disease in the pelvic area are major contributing factors.

Over-inflation of the balloon and/or bursting of the balloon are often mentioned as potential causes of intestinal perforation when performing transanal irrigation. However, it is just occasionally mentioned as the single causative factor when reviewing incident reports in applicable public databases. One of these databases is the 'Manufacturer and User Facility Device Experience Database' (MAUDE), a passive surveillance database hosted by FDA. Out of 43 incident reports between 1st January 2011 to 31st December 2015 for Peristeen, four reports involves a burst balloon as the specific or likely cause of intestinal perforation and in a few more cases it is mentioned that the user experienced problems due to a burst balloon, even though not resulting in a perforated bowel. However, there are probably a large number of unreported cases, especially when considering data reported by Christensen and co-workers; one out of three Peristeen users experienced balloon burst during irrigation.

Autonomic dysreflexia (AD) is a potentially life-threatening acute condition requiring immediate emergency care. AD most typically occurs in the SCI population, especially those with a lesion at or above the T6 spinal cord level. Acute AD is a reaction of the autonomic nervous system to overstimulation and is characterized by paroxysmal hypertension with throbbing headaches, profuse sweating, nasal stuffiness, flushing of the skin above the level of the lesion, slow heart rate, anxiety, and sometimes by cognitive impairment. AD is believed to be triggered by afferent stimuli (nerve signals that send messages back to the spinal cord and brain) which originate below the level of the spinal cord lesion. The most common causes of autonomic hyperreflexia seen in patients with SCI are loss of bowel and bladder function, resulting in impaction in the case of the bowels and distention in case of the bladder. Proper treatment of AD involves administration of anti-hypertensives along with immediate determination and removal of the triggering stimuli. The rectum should be cleared of stool impaction, using lubricating gel. If the noxious precipitating trigger cannot be identified, drug treatment is needed to decrease elevating intracranial pressure until further examination can identify the cause.

In the only randomized controlled study to date, investigating TAI, symptoms related to AD tended to be more common in the non-TAI group, potentially suggesting that TAI may have a protective effect against AD.

Additional difficulties that may arise during irrigation are e.g.; bleeding, pain, autonomic symptoms (sweating, palpitations and dizziness), leakage of water around the catheter/cone, difficulties inserting catheter/cone or instilling irrigant, retention of the instilled irrigant, no evacuation of stool after the TAI procedure, faecal incontinence and/or leakage of irrigant between TAI procedures.

A TAI procedure should always be carried out with caution. Bowel perforation is an extremely rare, but serious and potentially lethal complication to TAI, and will require immediate admission to hospital. A patient must contact the study investigator immediately if, during or after anal irrigation, he or she experiences any of the following:

- Severe or sustained abdominal pain or back pain, especially if combined with fever.
- Severe or sustained anal bleeding.

## 2 STUDY OBJECTIVES

### 2.1 Primary Objective

The primary objective of this study is to evaluate change in neurogenic bowel dysfunction symptoms between baseline and 3 months use of the Navina™ Smart system, as measured by a patient friendly version of the validated instrument NBD Score.

### 2.2 Secondary Objectives

The secondary objectives and outcome variables are shown in the table below:

**Table 1 Secondary Objectives**

| Secondary Objective                                                                                                             | Secondary Outcome Variable                                           |
|---------------------------------------------------------------------------------------------------------------------------------|----------------------------------------------------------------------|
| To investigate the change of QoL status in the selected patient population (absolute values)                                    | EQ-5D-3L variables                                                   |
| To investigate NBD symptoms after 6, 9 and 12 months use of Navina Smart system                                                 | NBD score                                                            |
| To investigate study product compliance                                                                                         | PRO variables (“Do you still perform TAI with Navina Smart?” Yes/No) |
| To investigate patient perception and satisfaction of bowel management including TAI therapy and use of the Navina Smart system | PRO variables                                                        |
| To investigate frequency of UTI                                                                                                 | PRO variables                                                        |
| To perform health economic analyses using QoL data and PRO variables                                                            | EQ-5D
PRO variables                                               |

### 2.3 Safety Objectives

The safety objectives and variables are shown in the table below:

**Table 2 Safety Objectives**

| Safety Objective                                                   | Safety Variables                                                     |
|--------------------------------------------------------------------|----------------------------------------------------------------------|
| To evaluate short- and long-term safety of the product and therapy | Adverse events, serious adverse events, adverse device effects, etc. |

## 3 STUDY DESIGN

### 3.1 Overall study design

This Clinical Study Protocol has been subjected to a peer review according to WHC standard procedures.

This study is designed as an open, prospective, non-controlled, qualitative, multicentre study of a novel system for TAI performed in a population of 150 subjects suffering from spinal cord injury, both traumatic and non-traumatic, and confirmed NBD. The main objective is to evaluate the change in NBD symptoms between baseline (before treatment start) and 3 months use of Navina Smart system.

Secondary objectives are to investigate the change of quality of life between baseline (before treatment start) and 3 and 12 months use of Navina Smart respectively, to evaluate improvements regarding constipation, faecal incontinence and frequency of patient reported UTIs, evaluate system compliance, and reasons for non-compliance, perception/satisfaction of the product and therapy as well as short- and long-term efficacy and safety at each follow-up; 3, 6, 9 and 12 months, respectively.

The study is expected to last for a total of 1 year for each subject, with a planned 12 months recruitment period and three scheduled site visits (Baseline, 3 months and 12 months). However, as the yearly incidence of subjects who are considered for TAI treatment is somewhat uncertain, it is recognized that the recruitment period may be prolonged until a sufficient number of evaluable subjects have been reached.

Data will be entered into electronic Case Report Forms (eCRFs) using Viedoc, a web based EDC system. At each irrigation episode, data will be stored in the Navina Smart system unit. The subject will transfer this data to the investigator via a compatible smartphone or tablet using the Navina Smart app.

#### **The patient population**

Spinal Cord Injury (SCI) may be traumatic or non-traumatic including infection, inflammation, compromised blood supply, post-ischemic etc., and may be referred to as a spinal cord lesion. The abbreviated term SCI will be used throughout the protocol to represent spinal cord damage of any aetiology. Approximately 150 male and female subjects following at least 3 months after the injury, treatment-naïve to TAI, 18 years and above and suffering from confirmed NBD will be consecutively screened and assigned to TAI with the Navina Smart system. The planned number of subjects will be recruited from 10-12 SCI centres in approximately 9 European countries. Subjects will be screened prospectively in both inpatient and outpatient settings according to the inclusion- and exclusion criteria stated in sections **4.2** and **4.3** of this protocol.

### 3.2 Study Visits

#### **Visit 1 – Baseline**

After explaining the study purpose, risks and benefits to the potential subject, the investigator shall allow the subject time to carefully consider participation in the study and to ask any questions about it. After obtaining the subject's signed Informed Consent and verifying that the

subject fulfils all inclusion and none of the exclusion criteria, the subject will be enrolled in the study and allocated a Subject ID in a consecutive order.

**NB: In the presence of a symptomatic UTI a potential subject *should not be enrolled* (see exclusion criteria no 10). After successful treatment of a UTI, the subject may be rescheduled for visit 1 in order to re-evaluate study participation.**

The original ICF will be stored in the Investigator's Study File (ISF) and a copy will be given to the patient.

At Visit 1, study site personnel will:

- Collect baseline demographics data as well as medical and surgical history and register in the eCRF.
- Document extent and severity of the spinal cord injury according to the American Spinal Injury Association (ASIA), as ASIA score A, B, C, or D in the eCRF.
- Provide subject with instruments for the collection of primary and secondary endpoints to be completed by the subject:
  - NBD score, **See section 6.4.1**
  - EQ-5D-3L, **See section 6.4.2**
  - Baseline Questionnaire, **See section 6.4.3**
- Train the subject in TAI management as a concept and in the Navina Smart system in particular. **See section 5.2**
- Dispense study products according to the “Component list and Supply scheme”. **See section 5.1.1**
- Make sure the subject has a compatible mobile device with the Navina Smart app installed and configured. **See section 5.1.2**
- Schedule a telephone contact one week after Visit 1.
- Schedule visit 2 (3 months follow-up).
- Update the subject's medical records with information about study participation, including the study code, a brief description of the study and the date subject signed the ICF.

**Weekly Telephone follow-up**

- Investigator or delegate will make a telephone call to the subject once per week until a feasible and satisfactory routine has been established, as agreed by both subject and investigator or delegate. The follow-up phone calls will be initiated by the therapist with the intention of identifying optimal performance and outcomes of irrigation, based on irrigation reports sent to site by the subject. If there are specific problems reported by the patient, or there is inadequate efficacy of treatment the therapist will advise tailoring of the TAI regime according to the Navina Treatment Schedule (see Appendix C). The health

status and compliance to the therapy will be monitored and collection of any AE and SAE will be performed.

## **Visit 2 – 3 months follow-up**

### **At Visit 2, study site personnel will:**

- Provide subject with instruments for the collection of primary and secondary endpoints to be completed by the subject:
  - NBD score, **See section 6.4.1**
  - EQ-5D-3L, **See section 6.4.2**
  - Follow-up Questionnaire, **See section 6.4.4**
- Document any AE/SAE and any changes in additional medications in the eCRF.
- Dispense study products according to the “Component list and Supply scheme”. **See section 5.1.1**
- Schedule the 6 and 9 months telephone follow-up.

## **Telephone follow-up**

- Investigator or delegate will make a telephone call to the subject at 6 and 9 months follow-up. The follow-up phone calls will be initiated by the therapist with the intention of confirming optimal performance and outcomes of irrigation, based on irrigation reports sent to site by the subject. If there are specific problems reported by the patient, or there is inadequate efficacy of treatment the therapist will advise tailoring of the TAI regime according to the Navina Treatment Schedule (see Appendix C). The health status and compliance to the therapy will be monitored and collection of any AE and SAE will be performed.
- Schedule visit 3 (12 months follow-up).

## **Visit 3 – 12 months follow-up and Study Termination**

### **At Visit 3, study subject will:**

- Return remaining study products.
- Return the borrowed Smartphone (if borrowed at baseline).

### **At Visit 3, study site personnel will:**

- Provide subject with instruments for the collection of secondary end points to be completed by the subject:
  - NBD score, **See section 6.4.1**
  - EQ-5D-3L, **See section 6.4.2**
  - Follow-up Questionnaire, **See section 6.4.4**

- Document any AE/SAE and/or changes in additional medications in the eCRF.
- When all questionnaires have been completed and all data entered into the study database, terminate the subject from the study in eCRF (Viedoc).

Study Flowchart

[figure not shown]

**Table 3 Study Plan**

|                                                | Visit 1
Baseline | Weekly
telephone
follow-up | Visit 2
3 months follow-
up
(± 2 w) | 6 months
telephone
follow-up
(± 2 w) | 9 months
telephone
follow-up
(± 2 w) | Visit 3
12 months follow-up
and Termination
(± 2 w) |
|------------------------------------------------|---------------------|----------------------------------|----------------------------------------------|-----------------------------------------------|-----------------------------------------------|--------------------------------------------------------------|
| Visit Window                            |                     |                                  |                                              |                                               |                                               |                                                              |
| Informed Consent and Subject demographics      | X                   |                                  |                                              |                                               |                                               |                                                              |
| Medical/Surgical history                       | X                   |                                  |                                              |                                               |                                               |                                                              |
| Inclusion/Exclusion criteria                   | X                   |                                  |                                              |                                               |                                               |                                                              |
| Disease specific severity score                | X a      |                                  |                                              |                                               |                                               |                                                              |
| NBD symptoms                                   | X b      |                                  | X b                               | X b                                | X b                                | X b                                               |
| Training/ Education on Navina Smart            | X                   |                                  |                                              |                                               |                                               |                                                              |
| Product dispensation                           | X                   |                                  | X                                            | X                                             | X                                             |                                                              |
| Telephone follow-up                            |                     | X c                   |                                              | X d                                | X d                                |                                                              |
| Smartphone dispensation                        | X e      |                                  |                                              |                                               |                                               |                                                              |
| AE/ADE/SAE/SADE                                | X                   |                                  | X                                            | X                                             | X                                             | X                                                            |
| Quality of Life f                   | X                   |                                  | X                                            |                                               |                                               | X                                                            |
| Evaluating current bowel care                  | X g      |                                  |                                              |                                               |                                               |                                                              |
| Evaluating Navina Smart system and TAI therapy |                     |                                  | X h                               |                                               |                                               | X h                                               |

a ASIA scale,

b NBD score

c Weekly telephone call until patient has an established routine

d Telephone Follow-up at 6 and 9 month use of Navina Smart

e Bluetooth Low Energy protocol (also called Bluetooth Smart or Version 4.0+ of the Bluetooth)

f EQ-5D-3L

g Baseline Questionnaire

h Follow-up Questionnaire

### 3.3 Study Design Rationale

Transanal irrigation of the bowel can be defined as a process of facilitating evacuation of faeces from the rectum and descending colon by passing water into the bowel via the anus. Two recent reviews have suggested that in individuals with chronic NBD, irrigation outperforms more conservative methods, reducing faecal incontinence and constipation, and as a consequence also improves self-reported quality of life. However there is currently lack of evidence identifying robust criteria for suitability, the impact of long term use on colonic function and reason for poor compliance over time. Thus, we have designed an open, prospective, non-controlled, qualitative multicentre study with the primary objective to evaluate the change in NBD score after use of the novel Navina Smart system. The assumption is that the NBD symptoms are constant over time (i.e. 12 months of study duration) if not treated in any way. The hypothesis in the present study is that any change in NBD Score is because of use of the Navina Smart system and hence no control group is required.

Secondary objectives are e.g. to evaluate compliance (and reasons for non-compliance) to the therapy and study product; change in QoL and patient-reported efficacy and safety. In addition, the study is intended to assess whether the use of Navina Smart unit and Navina Smart app, in terms of flexibility in tailoring irrigation regimes, is potentially associated with enhanced outcomes and greater patient tolerability. By synchronizing the Navina Smart unit with the Navina Smart app, a number of irrigation related variables (e.g. balloon size, water amount, instillation flow rate etc.) will be extracted and e-mailed by the subject as reports to the investigator or other designated study personal. This is to empower the patients in their treatments and illuminate the potentially enhanced outcomes and greater patient tolerability. Due to the nature of the therapy itself, it is not regarded as possible to adopt a blinded design approach. Since the product is CE-marked, based on similarities to existing products and concept, a single arm study design with each study subject acting as its own control has been chosen. Within the population suffering from SCI and a concurrent NBD there is a relatively low incidence of individuals considered for TAI and therefore a multicentre approach is deemed necessary. Otherwise there is a potentially high risk for a prolonged recruitment period.

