### 4.2 Inclusion Criteria

For inclusion in the study subjects must fulfil all of the following criteria:

1. Provision of informed consent.
2. Male or female aged 18 years or older.
3. Patient with previously confirmed chronic spinal cord injury, **either:**

- a) Traumatic; at any level and any completeness of injury and ASIA grade classification,
  - or
  - b) Non-traumatic; due to infection, inflammation (i.e.; transverse myelitis or ischaemic myelitis), compromised blood supply, a post-ischemic state, etc.
- 4. At least 3 months post spinal cord injury at time of consent.
  - 5. NBD score  $\geq 10$ , confirmed at Baselinea.
  - 6. Only TAI treatment - naïve patient (not having previously used any particular transanal irrigation system, e.g. Peristeen®).
  - 7. Confirmed NBD refractory to conservative therapy and judged eligible for transanal irrigation as per standardised treatment pathway.
  - 8. Able to handle smartphone/tablet.

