### 4.3 Exclusion Criteria

Any of the following is regarded as a criterion for exclusion from the study:

- 1. Any confirmed or suspected diagnosis of anal or colorectal stenosis, active inflammatory bowel disease, acute diverticulitis, severe diverticulosis, colorectal cancer, ischemic colitis, history of life-threatening autonomic dysreflexia, bleeding disorders, unspecified peri-anal conditions.
- 2. Untreated rectal impaction.
- 3. Any radiotherapy to the pelvis.
- 4. Any current treatment with anticoagulants (not including aspirin or clopidogrel).
- 5. Any current treatment with long-term systemic steroid medication (not including inhalation agents and/or local topical treatment).
- 6. Current use of prokinetics.
- 7. Any prior rectal or colorectal surgery within 3 months
- 8. Anal, rectal and/or colonic endoscopic polypectomy within the previous 4 weeks.
- 9. Overt or planned pregnancy.
- 10. Ongoing symptomatic UTI as judged by investigator.
- 11. Diagnosed psychiatric illness, considered as unstable by the investigator.

---

a An enrolled subject scoring  $<10$  on the Baseline NBD Score should be discontinued from the study.

12. Diagnosed with MS.
13. Involvement in the planning and conduct of the study (applies to both WHC staff and staff at the study site).
14. Previous enrolment in the present study.
15. Simultaneous participation in another clinical study that may interfere with the present study.

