**Table 6 Outcome Variables**

| Objective                                                                                                     | Outcome Variable | Method                                                                                                                                                                                                                                                          |
|---------------------------------------------------------------------------------------------------------------|------------------|-----------------------------------------------------------------------------------------------------------------------------------------------------------------------------------------------------------------------------------------------------------------|
| To investigate change in NBD symptoms between baseline and 3 months use of Navina System (primary objective). | NBD score.       | Analyses of absolute values and change between measurements according to instructions from the provider of the validated Neurogenic Bowel Dysfunction Score  (NBD Score) at Baseline (Visit 1) and 3 months (Visit 2).
See section 6.4.1 |

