The chosen minimal important difference for the study is related to the fact that also small difference could be clinically meaningful for the patients. In addition, depending on baseline NBD score level, smaller, but still valid, changes may be present when starting at a level closer to the inclusion cut of 10 than if the starting point is around 14. For this reason we believe a minimal important difference level valuable to detect in the study of ~0.8 would be representative.

Christensen et al describe in their sample published in 2008 a mean difference in NBD score of -4.5 with corresponding 95% confidence interval of -6.6 to -2.4 after introducing TAI for a 10 weeks' period. This indicates that the expected standard deviation for the difference between baseline and follow up in NBD score would lie somewhere around 2.1-2.2. For detection of a minimal important difference of 0.8, with an expected standard deviation of 2.2, a total of 80 (90% power) subjects who has been using Navina Smart for 3 months are required. However, since higher variability than expected and high drop-out rates may risk the final numbers additional patients must be accounted for. For example, Gosselink et al. reported a discontinuation rate of 55% when introducing TAI therapy in their sample reported in 2004 and Christensen et al. observed a discontinuation rate of 45%, why it is recommended to recruit at least 150 patients in the current study. This will allow 70 of 150 (47%) to drop-out from the study with maintained 90% power to detect a difference of 0.8 between a baseline NBD score (without Navina Smart) and after using Navina Smart for 3 months.

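### The Visit 1 NBD score both selects subjects and is the baseline for change, so some fall is expected without any device effect, yet section 3.3 credits any change to the device

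*Protocol*

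**What the plan says.** **Selection.** Inclusion criterion 5 (section 4.2) requires an NBD score of at least 10, confirmed at Baseline. The footnote, printed with section 4.3, says that an enrolled subject scoring below 10 "on the Baseline NBD Score should be discontinued from the study".

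**Reference for change.** Table 6 defines the primary outcome from the NBD score at Visit 1 and at 3 months. The study plan (Table 3) shows no NBD score before Visit 1, no run-in and no second baseline.

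**Comparison.** Section 3.3 says that "a single arm study design with each study subject acting as its own control has been chosen", and section 7.3 uses the Wilcoxon signed-rank test, so the null is zero change. Section 7.2 restricts the ITT set to correctly included patients, so the cut at 10 applies to both the PP and the ITT analysis.

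**Attribution.** Section 3.3 states: "The assumption is that the NBD symptoms are constant over time (i.e. 12 months of study duration) if not treated in any way". It then concludes that "any change in NBD Score is because of use of the Navina Smart system and hence no control group is required". The Objectives paragraph of the synopsis makes the same attribution, without the clause about a control group.

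**Population.** Criterion 4 reads "At least 3 months post spinal cord injury at time of consent". Criterion 3 requires chronic injury, and criterion 7 requires "Confirmed NBD refractory to conservative therapy and judged eligible for transanal irrigation". Section 4.4 allows stable laxative use, which should not be altered during the study.

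**The concern.** When subjects enter because a noisy score is at or above a cut-off, some are there partly because of a chance high reading. On retest their mean moves back towards the source mean. Because the selecting score is also the baseline, all of that movement counts as improvement. Using each subject as their own control does not help, since the artefact lies in the subject's own baseline.

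The argument that no control is needed rests wholly on constancy of untreated symptoms. That premise carries no citation. It is conditional on no treatment of any kind, whereas subjects come from conservative therapy and may stay on laxatives. It is also applied to patients from 3 months after injury.

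At stake is the meaning of a small but significant primary result. The study is sized to detect 0.8 points, and a change of that order could be reported as a device effect on the strength of section 3.3.

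**Working it through.** **1. The protocol's own figure.** Section 7.4 uses N = (Zα + Zβ)² σ² / μ₁². With 1.96, 1.28, σ = 2.2 and μ₁ = 0.8:

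(3.24)² × 4.84 / 0.64 = 79.4, rounded up to 80.

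This reproduces, and so does the allowance of 70/150 = 47% dropout. The sample-size arithmetic is not at issue.

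**2. Model for the artefact.** Assume a stable true score, no device effect, roughly normal scores with source mean m and SD s, test-retest correlation r, and selection at 10 or more. Then:

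- a = (10 − m)/s
- expected fall = (1 − r) × s × φ(a)/[1 − Φ(a)]

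The cut-off is the protocol's. The values of m, s and r are assumptions, because the protocol gives none of them.

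**3. Worked example, m = 12, s = 6.** a = −0.333, φ(a) = 0.377, 1 − Φ(a) = 0.631, ratio 0.598. The excess of the selected mean over the source mean is 6 × 0.598 = 3.59.

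| r | Expected fall |
|---|---|
| 0.9 | 0.1 × 3.59 = 0.36 |
| 0.8 | 0.2 × 3.59 = 0.72 |
| 0.7 | 0.3 × 3.59 = 1.08 |

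Over m = 10 to 14, s = 5 to 7 and r = 0.6 to 0.9, the fall runs from 0.18 (m = 14, s = 5, r = 0.9) to 2.23 (m = 10, s = 7, r = 0.6).

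**4. Holding the protocol's SD of the difference.** An SD of 2.2 fixes the reliability, since 2.2² = 2s²(1 − r) gives r = 1 − 4.84/(2s²). This is 0.903, 0.933 and 0.951 for s = 5, 6 and 7.

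| m | s | r | Expected fall |
|---|---|---|---|
| 10 | 5 | 0.903 | 0.39 |
| 12 | 6 | 0.933 | 0.24 |
| 14 | 7 | 0.951 | 0.16 |

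These rows include the largest and smallest values over the same m and s. All are at most about half of 0.8.

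**5. Chance of p < 0.05 with no device effect, n = 80.** By normal approximation the probability is about Φ(fall × √80/2.2 − 1.96), plus a negligible opposite tail.

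- Fall 0.39: 0.39 × 8.94/2.2 ≈ 1.58, so about 35%.
- Fall 0.16: 0.16 × 8.94/2.2 ≈ 0.65, so about 10%.

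The nominal rate is 5%. At the lower assumed reliabilities the SD of the difference is larger, but so is the fall. With m = 12, s = 6, r = 0.8 (SD of the difference 3.69), the chance is 41%, or 37% by Wilcoxon simulation on integer scores bounded at 0 and 47. With m = 14, s = 6, r = 0.9, it is 14% (12% by simulation).

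**The case against.** The strongest reply is that the protocol's expected SD of 2.2 implies high reliability, so the artefact is small. That stands as far as it goes, and is why step 4 is shown. Two things limit it. Even then the false-positive rate is two to seven times nominal. And 2.2 is itself weakly supported: section 7.4 draws 2.1 to 2.2 from a confidence interval of -6.6 to -2.4, whose half-width is (6.6 − 2.4)/2 = 2.1. A half-width reflects the standard error of a mean, not the SD of individual differences. A larger SD would mean lower reliability and a larger fall.

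A second reply is that chronic injury, refractory NBD, unaltered laxatives and the bars on prokinetics and on starting opioids restrain real change over time. This is fair. These rules limit drift and may raise the source mean, which weakens the truncation. They do not remove regression to the mean.

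A third is that the protocol openly calls the study non-controlled, labels these statements an assumption and a hypothesis, and sets the objective as evaluating change. That is also fair: the single arm is a disclosed choice for a CE-marked product. The objection here is to the step from assumption to attribution, and to the clause that a control is therefore unnecessary.

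The words confirmed at Baseline might suggest an earlier qualifying score, but none is scheduled or used as the reference. Section 7.4 shows that the authors had the cut-off in mind, noting that "smaller, but still valid, changes may be present when starting at a level closer to the inclusion cut of 10", without considering its effect on the baseline.

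**Conclusion.** The point holds. Selection and baseline share one score, so a fall is expected with no device effect, and the attribution in section 3.3 and the synopsis does not follow from the design. Under a normal model with a stable true score, source mean 10 to 14 and SD 5 to 7, the fall is about 0.16 to 0.39 points with the protocol's 2.2 held, and 0.2 to 2.2 points at reliability 0.6 to 0.9.

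A reader might infer more than this. The documents do not support the following:

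- **That regression to the mean alone is about as large as the 0.8-point target.** This needs a reliability near 0.8 or below over much of the range, which the protocol neither gives nor implies.
- **That a large improvement would be an artefact.** A change near the cited -4.5 lies well beyond every value computed here.
- **A figure for recovery after recent injury.** Nothing in the protocol gives the share of recently injured subjects or their rate of change, so this drift is possible but cannot be sized.
- **That subjects inflate scores to obtain the device.** No section says that they are told the cut-off, and the device is commercially available.
- **That time since injury is not recorded.** Section 6.1 does not list it separately, but it may fall under medical history, and criterion 4 cannot be verified without it.

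**What to change.** 1. **Wording.** In section 3.3 and the synopsis, remove the statement that any change is because of the device. In section 3.3, also remove the clause that no control group is required. Limit the conclusion to uncontrolled within-subject change from baseline, and state that regression to the mean may account for some or all of a change near 0.8 points. This costs nothing beyond an amendment and can be done even after enrolment has begun.

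2. **Separate the two scores, where feasible.** Use one NBD score for eligibility. Take the analysis baseline from a second score, completed on a separate day before training and dispensing, and remove no one on the second score. The separate day matters: two scores at the same visit would share transient error and recalled answers, and little regression would be removed. The cost is one more 10-item questionnaire and a short delay before training, since Visit 1 now combines consent, questionnaires, training and dispensing.

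3. **Time since injury.** Report the primary change by time since injury as a sensitivity analysis, using the injury date already needed to verify criterion 4. The cost is one extra analysis and, if the date is not already in the eCRF, one field.
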